#### NET protocol

Firstly, the participants were evaluated for a healthy deltoid muscle, capable of resisting the testing pressure of the practitioner. The participants were seated, and asked to raise their arm 90 degrees to their body, keeping their elbow straight. Pressure was applied to the participant's wrist, whilst they were asked to "hold strong", (i.e. resist pressure). A practice trial was conducted to familiarize the participants with muscle testing procedure (MTP). This MTP has shown good inter-examiner reliability [67].

The participants were asked to make the following statement, "I'm OK, keeping still."

If MTP to this statement tested weak, it is said that the participant is non-congruent with that concept.

Next, the participants were asked to continually repeat that statement whilst the practitioner continued the MTP with one hand and with the other hand palpated the different meridian access points (MAPs) on the participant's body. Each MAP is considered to be a specific skin point which, based on acupuncture theory is associated with certain emotions [68]. (Figure 2 and 3)

**Figure 2 F2:**
[figure not shown]
**NET Body Meridian Access Points (MAPs)**.

**Figure 3 F3:**
[figure not shown]
**Simplified Master NET Chart outlining Meridians/Organs; Subluxation sequences; Emotions; NET Remedies**.

When the participants tested strong to the statement and a MAP, it was considered that there was an emotional component related to their problem.

The practitioner continued to explore the psychosomatic connection by making a series of statements. Using the MTP the concept of an "original event" was being investigated. The current "emotion" was related to a past event by the asking of "when, where, and who" questions. This was done to uncover why there appeared to be retained conditioned response to a previous stressful event.

The untested theory of NET suggests that the stimuli associated with the original event become associated via a process of Pavlovian conditioning, and are then reproduced through a process of repetition compulsion.

The participants were provided a statement that connected past and present events relating to their "emotion". If the MTP using this statement, tested weak, it indicated that the problem had been recalled.

Next, the participants were asked to contemplate the original event and associated feelings in the conscious mind, and were given kinaesthetic stimulation of spinal segments. The conscious recall of past events with the association of normalised stimuli is theorised to condition the original event with positive stimuli. This is believed to break the cycle of the conditioned (learnt) response by reactivating the original negative event and it's ongoing repetition and pairing it with a competing somatic stimulus.

Lastly, the practitioner retested the participant by using MTP to check the original statement "I'm OK keeping still". When the MTP tests strong, this indicates the participant is now congruent with that statement.

This procedure was repeated using 16 different referential statements. During the first month of treatment two referential statements per visit were used and tested. If the MTP tested weak, implying the participant was not congruent with the concept in that particular statement, then the NET protocol ensued. Please see Table 1 for a complete list of statements used. The statements were designed by the primary investigator in consultation with an expert NET practitioner and the study supervisors using the DSM-IV criteria which are used to diagnose ADHD and coupled them with the standard 15 step NET protocol (Figure 1), designed by Walker [40]. Another explanation of this protocol is described in a study published by Bablis and colleagues [50].

**Table 1 T1:** List of referential statements used in NET protocol for treatment group B.

**Referential statements**	**Muscle testing procedure (MTP)**	
	**Non-congruent (weak muscle)**	**Congruent (strong muscle)**

I'm OK having ADHD		

I'm OK keeping still		

I'm OK listening to authority		

I'm OK waiting my turn		

I'm OK thinking one thing at a time		

I'm OK thinking before doing		

I'm OK remembering what I'm told		

I'm OK finishing what I start		

I'm OK doing homework		

I'm OK doing class work		

I'm OK listening to the teacher		

I'm OK doing school work		

I'm OK thinking before talking		

I'm OK staying in my seat		

I'm OK having quiet time		

I'm OK going to sleep at bedtime		

### Sham NET protocol

The sham protocol was designed to mimic the real NET treatment protocol, however without the therapeutic benefits. The sham protocol incorporated the MTP throughout the procedure, with different sets of statements and tapping on the back. The set of statements used were not related to the treatment protocol, but instead used for testing of congruent and non-congruent reactions to statements like, " my name is John" and then "my name is Robert" i.e. the child's name first then another name. See Table 2 for a complete list of the first Sham protocol. In total eight different sham protocols were designed with different lists of referential statements.

**Table 2 T2:** List of referential statements used in sham protocol for sham group A.

**Referential statements for sham**	**Muscle Test**	
	**Weak**	**Strong**

My name is .......... (insert child's name)		

My name is .......... (make up wrong name)		

My age is ............ years (insert child's age)		

My age is ............ years (insert wrong age)		

I live in ............... (insert child's suburb)		

I live in .............. (insert wrong suburb)		

Today is ............. (insert the name of today)		

Today is ............. (insert the wrong day)		

My hair colour is .... (insert colour of child's hair)		

My hair colour is .... (insert wrong colour of child's hair)		

My eye colour is .... (insert colour of child's eyes)		

My eye colour is .... (insert wrong colour of child's eyes)		

I am in ............... class at school (insert child's class)		

I am in ............... class at school (insert wrong class)		

I go to ................ (insert name of child's school)		

I go to ................ (insert name of wrong school)		

My teachers name is .... (insert name of teacher)		

My teachers name is ... (insert wrong name of teacher)		

My favourite sport is ... (insert name of favourite sport)		

My favourite sport is ... (insert name of wrong sport)		

My favourite subject at school is ... (insert favourite subject)		

My favourite subject at school is ... (insert wrong subject)		

My worst subject at school is ... (insert worst subject)		

My worst subject at school is ... (insert different subject)		

My best friend is ... (insert name of best friend)		

My best friend is ... (insert wrong name)		

### Risks

As there are no known side effects and there have not been any reports of adverse reactions to the NET protocol, we do not anticipate that any participants will be exposed to any unnecessary risks. However, in the event that a child becomes emotionally distressed during the protocol, the procedure will be terminated. Support counselling will be offered by qualified psychotherapists and counsellors for the child at no expense to the parents. These professionals have all been approved for the study by the university Ethics Committee and have also undergone background screening and have been approved to work with children.

### Ethics review

The trial protocol was reviewed by the Macquarie University Human Ethics Committee (Sydney, Australia) and was granted Human Ethics Approval (HE26AUG2005-M04261). As a prerequisite to conducting research with children, the Ethics committee required all those involved with the study undergo background screening as part of the "Working With Children Check". All those involved in the study were approved and ethics was granted.

Furthermore, as part of this study, an application was made to the Department of Education and Training and a State Education Research Approval was granted (SERAP #06.350). This enabled the researchers to send questionnaires to the teachers of the participants of the study.

### Informed consent

All of the parents of the participants were issued with two copies of the informed consent forms (one to keep and one to return to the university). The informed consent form conveyed the following information: the names of the chief investigator, the supervisors and the four practitioners administering the interventions; the name of the university and the department conducting the research; a brief description of the control, treatment and sham groups; the duration of the study; the questionnaires used; the Ethics approval and contact details of the Ethics officer; the right to withdraw their child at any time; in the event a child becomes distressed the back-up counselling services available; the involvement of teachers; and the fact that the results of the study will be disseminated via conferences and publications whilst maintaining the children's privacy.

### Analysis

Demographic and baseline characteristics of participant variables will be compared between the three randomised groups using the Restricted Maximum Likelihood (REML) in GenStat 10^th ^Edition [69].

The primary analysis will compare outcomes for each primary and secondary outcome measure between the three groups (treatment, sham and control) using the Restricted Maximum Likelihood (REML) in GenStat 10^th ^Edition [69], to estimate treatment effect with 95% CI. REML is a method for fitting mixed linear models (the models for ANOVA being special cases) which can produce unbiased (or less biased) estimates of variance and covariance parameters. This is a relatively new and powerful technique that allows for data sets that are unbalanced, have missing values, have treatments with unequal variances and/or have correlated error terms [70].

An intention-to-treat (ITT) analysis will be undertaken of the one month and seven month data from the CPRS-R:L and CTRS-R:L for the participants who commenced the study but did not complete.

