### Measures

The Diagnostic and Statistical Manual of Mental Disorders ADHD diagnostic criteria [53,54] were used by the participants' Pediatricians and Clinical Psychologists to establish a diagnosis. The reliable and validated Conners' Parent Rating Scales-Revised Long Version (CPRS-R:L) and Conners' Teacher Rating Scales-Revised Long Version (CTRS-R:L) [55-59] were used pre and post intervention.

The ratings scales were administered pre-intervention to establish baseline data, and were used as outcome assessments to measure the intervention effects at the end of the first month and at the conclusion of the study i.e. in seven months. Of the 14 subscales described in the CPRS-R:L and the 13 subscales described in the CTRS-R:L, two were chosen as primary outcome measures (POMs) and three were chosen as secondary outcome measures (SOMs). Primary outcome measures included Conners' ADHD Index and Conners' Global Index Total subscales H and K respectively. The secondary outcome measures included DSM-IV:Inattentive, DSM-IV:Hyperactive-Impulsive and DSM-IV:Total, subscales L, M, and N respectively.

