### Treatment allocation

Eligible participants were randomly allocated to one of three groups A, B, & C (i.e. group A-sham, group B-treatment, and group C-control). The "QuickCalcs" program from the GraphPad Software [60] was used to randomly sequence 150 numbers (repeated 1×) into the three groups.

Each number and its randomised letter (A, B, or C) were placed in an opaque envelope. Each envelope was numbered consecutively from 1–150.

As each parent called to have their child screened they were allocated the next consecutive number once they were eligible, so that eligible participant no. 1 was allocated to envelope no. 1, etc. The screener was unaware of the sequence of group allocation at the time of screening, hence allocation was concealed at time of recruiting.

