### Sample size justification

Calculations for the sample size were set with a significance level of 0.05 and the power of 80%.

As there are no prior studies conducted in the area of chiropractic or NET for an ADHD cohort, for power analysis purposes a SD of 6.7 was adopted based on data from Shortt [61], yielding a sample size of 63. The value of 6.7 for power testing is supported by findings from a paper on the meta-analysis of RCTs in ADHD responses to atomoxetine using the CRS [62]. This study revealed an average SD score of 6.7, which is consistent with the SD found in the Shortt data [61]. In a meta-analysis of psychotherapy dropouts the mean attrition rate was 46.86% [63,64]. Based on this drop-out rate it was prudent to increase the sample size by this figure, increasing it from 63 to n = 93.

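### The only stated use of the baseline Conners' scores is a between-group comparison; the outcome model is not said to adjust for them, a free gain in precision whose size depends on an unstated correlation

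*Protocol article*

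**What the plan says.** All references are to the protocol article.

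- **Measures.** "The ratings scales were administered pre-intervention to establish baseline data", and the same parent and teacher scales are repeated at one and seven months. The two primary and three secondary outcomes are subscales of these instruments, so each has a baseline value.
- **Analysis, first paragraph.** "Demographic and baseline characteristics of participant variables will be compared between the three randomised groups", by REML. This is the only use of baseline that the section names.
- **Analysis, second paragraph.** Each outcome is compared between treatment, sham and control by REML, "to estimate treatment effect with 95% CI". Fixed effects and covariates are not listed. The text notes that the method copes with missing values and correlated errors.
- **Analysis, last paragraph.** The intention-to-treat analysis concerns the one-month and seven-month data.
- **Sample size justification.** An SD of 6.7 is used, "yielding a sample size of 63". This is raised to 93 because, in a meta-analysis of psychotherapy dropouts, "the mean attrition rate was 46.86" per cent. The article does not give a detectable difference or a baseline to follow-up correlation, and it does not say whether 6.7 is the SD of a raw score, a change score or an adjusted residual.

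**The concern.** Under randomisation, baseline differences between arms arise by chance. Comparing the arms at baseline describes those differences but does not remove them from the treatment estimate; a baseline covariate in the outcome model does. Baseline on the same scale and from the same rater is usually a strong predictor of the later score.

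The arms are small: 21 per arm planned, and about 16 or 17 if attrition is as the article expects. If the outcome comparison uses post-intervention scores alone, chance imbalance passes into the estimate and the 95% confidence interval is wider than it need be. An unadjusted randomised comparison remains unbiased, so what is at stake is precision and power, not validity.

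**Working it through.** **Inputs from the article:** alpha 0.05, power 80%, SD 6.7, 63 evaluable children, attrition 46.86%, 93 enrolled.

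**Assumptions:** two-sided test; 1:1:1 allocation; one pairwise comparison; a 6-point difference; dropouts contribute nothing; r as shown.

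**1. The article's own figures.** 63 × (1 + 0.4686) = 92.5, rounded up to 93, so 93 is reproduced. The base figure of 63 cannot be reproduced, because no difference is stated. Back-solving 21 per arm at 80% power gives 5.79 points (normal approximation) or 5.94 points (t test). The assumed 6 points is therefore close to what the plan implies; a t test with 21 per arm has 81% power for it.

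**2. Evaluable children at the stated attrition.** 93 × (1 − 0.4686) = 49.4, or 16.5 per arm, which is 49.4/63 = 78.4% of the number required.

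**3. If 6.7 is a raw-score SD.** Adjusted SD = 6.7 × √(1 − r²). Two-sided t-test power for 6 points at 16.47 per arm:

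| r | Residual variance kept (1 − r²) | Power |
|---|---|---|
| 0 (unadjusted) | 1.00 | 70.2% |
| 0.3 | 0.91 | 74% |
| 0.4 | 0.84 | 78% |
| 0.5 | 0.75 | 82.0% |
| 0.6 | 0.64 | 87.5% |
| 0.7 | 0.51 | 93.6% |

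Break-even with 63 unadjusted children requires 1 − r² ≤ 0.784, so r ≥ √(1 − 0.784) ≈ 0.46. This threshold does not depend on the assumed difference, but the power figures do. At 5 points, power is 55% unadjusted and 67%, 74% and 83% at r = 0.5, 0.6 and 0.7.

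**4. If 6.7 is a change-score SD.** Change-score variance is 2σ²(1 − r) and covariate-adjusted variance is σ²(1 − r²), so the ratio is (1 + r)/2. The comparator is now a change-score analysis, with the same 70% power at 16.5 per arm.

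| r | (1 + r)/2 | Power |
|---|---|---|
| 0.3 | 0.65 | 87% |
| 0.5 | 0.75 | 82% |
| 0.7 | 0.85 | 77% |

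Break-even requires (1 + r)/2 ≤ 0.784, so r ≤ 2 × 0.784 − 1 ≈ 0.57. Here the gain shrinks as r rises.

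**5. If 6.7 is already a baseline-adjusted SD.** The gain is already counted in the 63, and power at 16.5 per arm stays at about 70%.

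**The case against.** The strongest objection is that silence is not exclusion. The Analysis section lists no model terms at all, not even time. The scales are described as used before and after intervention, the Discussion speaks of monitoring changes in outcomes, and REML with correlated errors could carry baseline as a covariate, a repeated measure or a change score. An article may leave such terms to a fuller protocol or analysis plan. This stands against any reading that baseline is kept out of the outcome model: a reader might infer that, but the text does not say it. It does not dispose of the point. The section does assign baseline a use, and that use adds no precision to the treatment estimate. The other routes are also not all equivalent to a covariate: as step 4 shows, a change score is less efficient whenever r is below 1.

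A second objection is that the gain depends on figures the article does not give. This also stands. A range of r from 0.5 to 0.7 lies wholly above the raw-score break-even and would make the offset look assured, which it is not. The 49.4 further assumes that dropouts supply nothing, whereas one-month data from later dropouts, kept in a mixed model, would reduce the shortfall.

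A reader might also suspect that the baseline comparison will decide whether to adjust. No such rule is stated, so that is speculation and forms no part of the point.

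**Conclusion.** The point holds as a free improvement. The article collects a matching baseline for every outcome, names only a between-group comparison as its use, and does not state that it enters the REML outcome comparison. If the outcome comparison is an unadjusted one of post scores, a covariate would cut residual variance by r²: 9% at r = 0.3, 25% at 0.5 and 49% at 0.7.

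It is tempting to conclude that adjustment makes good the attrition shortfall. The article does not support that without conditions. It needs r of at least about 0.46 if 6.7 is a raw-score SD, r of at most about 0.57 if it is a change-score SD, and fails if the SD is already adjusted. All the power figures rest on the assumptions listed with the working.

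The inflation from 63 to 93 is a separate error. Dividing by the retained fraction gives 63/0.5314 = 118.6, or 119. Baseline adjustment does not correct that calculation.

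**What to change.** In the Analysis section, state that the REML model of the one- and seven-month scores includes the baseline score of the same subscale and the same rater as a fixed covariate. Present demographic and baseline characteristics descriptively by group, without between-group tests. In the Sample size justification, say what kind of SD 6.7 is, and give the assumed r if any credit for adjustment is taken.

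The cost is a line or two of text, with no additional data or participants. If a fuller protocol or analysis plan already specifies the covariate, one confirming sentence is enough.

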### Objectives

The objectives of this research are to:

1. To determine whether the addition of the Neuro Emotional Technique (a new biopsychosocial intervention), to an existing medical regimen can improve clinical outcomes (i.e. reduce inattention, hyperactivity and impulsivity) for children with medically diagnosed ADHD.

2. Furthermore, to determine the responses in the short term (i.e. one month) and medium term (seven months).

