#### Primary Outcome Measures

The Conners' ADHD Index is used to distinguish ADHD children from non-clinical children, and is considered a good screening tool [55,59]. The Conners' Global Index (CGI) is valuable in assessing general psychopathology and for monitoring treatment effectiveness and changes over time. It is sensitive to treatment changes for repeated measures [55,56]. It reflects general behavioral problems, including hyperactivity and attentional difficulties.

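### The primary analysis takes in every primary and secondary measure across three groups and names no primary test, while the sample size uses a single 0.05

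*Protocol article*

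**What the plan says.** The protocol article fixes the following.

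- **Scope (Analysis).** "The primary analysis will compare outcomes for each primary and secondary outcome measure between the three groups". The three groups are treatment, sham and control. The method is REML, estimating the treatment effect with a 95% CI. The same section says that one-month and seven-month data from both the parent and the teacher scale are analysed.
- **Measures (Measures).** Of the Conners' subscales, "two were chosen as primary outcome measures (POMs) and three were chosen as secondary outcome measures (SOMs"). The primary pair is the ADHD Index and the Global Index Total. Neither is ranked above the other, and neither is the parent or the teacher form.
- **Times (Objectives).** The second objective is "to determine the responses in the short term (i.e. one month) and medium term (seven months"). Neither time comes first.
- **Role of each index (Primary Outcome Measures).** The ADHD Index is "considered a good screening tool". The Global Index is described as useful for monitoring treatment and as responsive to treatment change on repeated measurement.
- **Size (Sample size justification).** The calculation uses "a significance level of 0.05 and the power of 80" per cent. Then "for power analysis purposes a SD of 6.7 was adopted", "yielding a sample size of 63", raised to 93 for dropout. No effect size, index, rater, time point or contrast is attached to these figures.

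**The concern.** The article separates primary from secondary measures in one section and puts both into the primary analysis in another. Even within the primary measures, two indices, two raters, two times and three groups all have equal standing. A reader of the results could not tell which comparison the trial was meant to decide.

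Two things are at stake. If each comparison is read at 0.05, the chance that some primary result is significant with no true effect is well above 5%. If a correction is added later, the power behind the sample size no longer applies.

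The contrasts also differ in quality. The Blinding section says that control-group parents knew their child's allocation, and parents complete one of the two rating forms. A parent-rated difference between NET and control is therefore open to rater bias in a way that NET versus sham is not. As written, the two have equal rank.

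**Working it through.** **1. The plan's own figure.** The 63 cannot be reproduced forwards because no effect size is given, so it was solved backwards. Assumptions: 63 is the total for three equal groups (21 per arm), the test is two-sided at 0.05, power is 80%, SD is 6.7.

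- Normal formula: δ = SD × (1.960 + 0.842) × √(2/21) = 6.7 × 2.802 × 0.3086 ≈ 5.8 points.
- The t-test gives 5.94 points.
- Reading 63 as a per-arm number would instead give 3.34 points (0.5 SD), so the 21 per arm used below is an assumption.

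**2. Number of comparisons.**

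- Primary measures: 2 indices × 2 raters × 2 times = 8 outcomes for any one contrast.
- With the three secondary measures, as the Analysis sentence is worded: 5 × 2 × 2 = 20.

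**3. Upper illustration.** If the 8 outcomes were independent, the chance of at least one p < 0.05 under no effect is 1 − 0.95⁸ = 0.337. They are correlated, so the true figure is lower.

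**4. Simulation with correlation.** Trials with no effect, 21 per arm, 8 primary outcomes. The article gives no correlations. The assumed ranges are 0.7–0.9 between indices, 0.3–0.5 between raters and 0.5–0.8 between times. The last column sets all three correlations at 0.9.

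| Chance of at least one false positive | Assumed range | All at 0.9 |
|---|---|---|
| NET versus sham, two-sided | 19–28% | 13–14% |
| NET better than sham only (nominal 2.5% for one test) | 10–14% | about 7% |
| Three-group test on each outcome | 20–28% | about 14% |

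**5. Cost of correcting afterwards.** Two-sample t-test, SD 6.7, 21 per arm, with the assumed difference of 5.8 to 6 points from step 1. Bonferroni over index × rater gives 0.05/4 = 0.0125; over index × rater × time it gives 0.05/8 = 0.00625.

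| Significance level | Power at 5.8 points | Power at 6 points |
|---|---|---|
| 0.05 | 78% | 81% |
| 0.0125 | 58% | 61% |
| 0.00625 | 48% | 51% |

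**The case against.** The strongest reply is that this is a condensed article. Adjustment methods and the order of testing commonly sit in a full protocol or analysis plan that is not shown, so their absence proves little. That stands, and the point does not rest on it. It rests on what the article does fix: a primary analysis that includes the secondary measures, two unranked primary indices, and one alpha for the sample size.

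Further replies have force.

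- **The per-test 0.05 is not written down.** It appears only in the sample size text. The Analysis section speaks of estimation with 95% CIs. Judging each comparison at 0.05 is an inference, though nothing suggests another threshold.
- **A reader might infer that the sample size was computed for one specific test.** The article names no test or contrast. It shows only one alpha, one SD and one N.
- **A reader might count every pairwise comparison:** 8 × 3 = 24 for the primary measures and 20 × 3 = 60 with the secondary ones, with error rates of about 40–74% in simulation. The article does not list pairwise tests. Those rates also count sham-versus-control differences and results against NET, and neither would be a success for NET. They should not be used as the size of this problem.
- **REML could model both times or test the groups jointly.** That would reduce the number of tests, but the sentence says *each* measure, so indices would still be separate, and no combination of raters is described. Requiring the three-group test first still leaves about 20–28%.
- **The first objective does state a question.** It asks whether adding NET improves outcomes. It does not identify one testable comparison.

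**Conclusion.** The concern holds in this form: the article defines an all-inclusive primary analysis and identifies no primary test, while the trial is sized on a single 0.05. If results are read at 0.05 each, the false-positive chance for NET versus sham over the 8 primary outcomes is about 19–28%. In NET's favour it is about 10–14%, four to nearly six times the nominal 2.5%. Very high correlation (0.9 throughout) lowers the two-sided figure to about 14% but does not remove the inflation.

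These sizes depend on the assumed correlations, on 63 being a three-group total, and on the inferred 0.05 threshold. The power loss also depends on a back-solved difference and illustrates the direction and rough scale only. A reader might go on to infer that success will be claimed on any combination of results. The article states no success rule, and one requiring both indices would behave differently, so that reading is not supported.

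**What to change.** Before any unblinded analysis:

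1. Name one primary test. The contrast should be NET versus sham, because the trial is placebo-controlled and control-group parents know their allocation. Fix one index, one rater and one time point. The Global Index is the natural choice on the article's own description of the two indices. Nothing in the article favours one rater or one time, so the sponsor should choose these without sight of results.
2. Test the remaining primary combinations of index, rater and time in a stated order, or with a stated split of alpha.
3. Delete *and secondary* from the primary-analysis sentence, and report the DSM-IV subscales as secondary with unadjusted 95% CIs.
4. State the effect size, test and contrast behind the 63, so that the sample size refers to the named test.

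This needs wording only and no new data. With a single named test at 0.05, multiplicity gives no reason to change the 63. The cost is that the other index, rater and time point lose equal primary status. The Recruitment section says the last participant finished in March 2008, so the choice comes after data collection. The report should state that it was made before unblinding; if that cannot be shown, the chosen primary test should be reported as post hoc.

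### The intention-to-treat sentence is wrong as written: it describes an analysis of children who started but did not finish, and does not tie the primary comparison to all randomised children

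*Protocol article*

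**What the plan says.** The Analysis section has two separate statements on the outcome comparison.

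- The primary analysis: "The primary analysis will compare outcomes for each primary and secondary outcome measure between the three groups (treatment, sham and control"), fitted by REML to give treatment effects with 95% confidence intervals. No analysis set is named. REML is favoured partly because it "allows for data sets that are unbalanced, have missing values".
- A later paragraph plans a further analysis, labelled ITT, of the parent and teacher scales at both follow-up times. Its stated scope is "for the participants who commenced the study but did not complete".

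Four other sections bear on this.

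- Sample size justification: "In a meta-analysis of psychotherapy dropouts the mean attrition rate was 46.86" per cent, and this rate is used to raise the sample from 63 to 93.
- Treatment allocation: as parents phoned for screening, "they were allocated the next consecutive number once they were eligible".
- Blinding: parents of control children knew that their child was in the control group and would be treated after the study.
- Recruitment: the last participant finished in March 2008. The Analysis section is nevertheless written in the future tense.

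**The concern.** ITT is defined by who was randomised and to which group. What happened afterwards does not enter into it. The sentence makes membership depend on two later events, starting and not finishing. A comparison among children selected on those events is no longer protected by randomisation, whatever model is fitted.

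The placement adds to the difficulty. Because ITT appears as a further analysis for non-completers, the reader cannot tell whether those children are already in the primary model. If they are, the extra analysis has no clear purpose. If they are not, the main result comes from completers. The text allows either, so the choice could be made after the results are known.

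This matters more here than in a trial with little loss. The planning attrition is close to half, and the arms differ in ways that could affect who leaves: sham and NET families attend 14 sessions (eight, then six), while control families knowingly wait. Reasons for leaving may therefore differ by arm.

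**Working it through.** **Inputs.** From Sample size justification: base sample 63, final sample 93, attrition 46.86%, SD 6.7, significance level 0.05, power 80%. No target difference is given. Assumed where needed: equal arms, equal attrition in each arm and a two-sided pairwise test.

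**1. The plan's own figure.** 63 × (1 + 0.4686) = 92.5, rounded up to 93. This matches the stated sample. (Whether that is the right way to allow for attrition is a separate question and is not used here.)

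**2. The sets that the wording could mean, out of 93.**

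| Reading | Children | Arithmetic |
|---|---|---|
| ITT sentence taken literally (non-completers) | about 44 | 0.4686 × 93 = 43.6 |
| Primary comparison, if run on completers | about 49 | 93 − 43.6 = 49.4, or 16.5 per arm |
| ITT in its ordinary meaning | 93 | all randomised |

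The figure of 44 is an upper bound for the literal set, because the word *commenced* removes any child who was allocated but never started. The number of such children cannot be derived from the article.

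**3. How a completer contrast can be biased.** Let a be the proportion lost in an arm, C the mean for completers and D the mean that drop-outs would have had. The full-arm mean is (1 − a)C + aD, so the completer mean differs from it by a(C − D). With the same a in two arms, the contrast shifts by

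bias = a × [(C − D) in one arm − (C − D) in the other].

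The bracket is unknown. Over an assumed range, at a = 0.4686 and SD 6.7:

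| Assumed between-arm difference in the gap | Shift in the contrast |
|---|---|
| 0.25 SD | 0.4686 × 0.25 × 6.7 = 0.8 points |
| 0.5 SD | 0.4686 × 0.5 × 6.7 = 1.6 points |
| 1 SD | 0.4686 × 1 × 6.7 = 3.1 points |

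If the gap is the same in both arms, the shift is zero.

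**4. A yardstick.** With 21 per arm (63 ÷ 3), the difference detectable at 80% power is 6.7 × (1.960 + 0.842) × √(2/21) = 5.8 points. Against this back-solved value the shifts are about 14%, 27% and 54%. A one-sided 0.05 test would imply 5.1 points and slightly larger fractions.

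**The case against.** The best defence is that the sentence is clumsy drafting. An ITT analysis of drop-outs alone would be a strange thing to plan, and the author may only have meant that children who start and do not finish will still be counted. The same section calls the groups randomised when describing the baseline comparison, puts no completer restriction on the primary analysis, and chooses a method that tolerates missing values. A condensed article may also leave analysis sets to a fuller document.

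Much of this stands, and it limits the point.

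- A reader might infer that the main comparison **is** confined to completers. The article does not say so; it only fails to rule this out. The missing definition of the primary set is not a finding in itself. The finding is that the one sentence which does define a set defines it wrongly.
- A reader might infer that reasons for leaving **do** differ by arm. The Blinding section shows only that control parents knew their status.
- A reader might infer that children were allocated before written consent or baseline ratings. Numbers were given once a child was eligible, and Participants lists written consent among the inclusion criteria, so the order is uncertain. Measures says only "The ratings scales were administered pre-intervention to establish baseline data", which does not place those ratings before or after allocation.
- The 46.86% is a mean from a psychotherapy meta-analysis, adopted for planning. Stopping sessions also need not mean that scales are missing; a plan to analyse later data from non-completers suggests that some were expected.

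The defence fails on one matter. REML's tolerance of missing values concerns how incomplete records are handled once in the model. It does not say whose records go in. An intended meaning that has to be guessed is not a fixed analysis set.

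**Conclusion.** Wrong as written. The sentence mis-defines ITT: taken literally it covers at most about 44 of 93 children, all non-completers, and omits any child allocated but never started. It leaves the primary comparison untied to the randomised groups, so a completer-only main result on about 49 children is possible though not stated.

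These counts rest on the article's own 46.86% and 93. The bias of a completer comparison cannot be sized from the documents. The range of 0.8 to 3.1 points is an illustration that assumes equal attrition in each arm and a gap difference of 0.25 to 1 SD, neither of which has a source in the article. If attrition differs between arms, the simple formula no longer applies. The 5.8-point yardstick is likewise back-solved, since no target difference is stated. The need for correction depends on the wording and not on any of these sizes.

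**What to change.** Replace the ITT sentence in the Analysis section with:

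> The primary REML analysis is by intention to treat: all randomised children, in the group allocated, using every available baseline, 1-month and 7-month CPRS-R:L and CTRS-R:L score in a repeated-measures model, whether or not they started or completed sessions. The missing-data assumption is stated, and any completer analysis is supportive.

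The missing-data statement is needed because a child with no follow-up score stays in the randomised set but adds little or no information on change. The result then depends on what is assumed about the unseen scores.

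The cost is wording only: no more children, visits or questionnaires. Changing when envelopes are assigned, or continuing to send scales to families who stop sessions, is not proposed, because enrolment and follow-up have ended according to Recruitment. The sentence can still be changed because the analysis is described as yet to be done. The change should be dated and should record whether outcomes by group had already been seen.
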